## Method

### Public and patient involvement

Adolescents were involved in the research since its inception. Adolescents were recruited via UNICEF and provided input on intervention design and development (*N* = 37, 73% girls, age range = 13–19 years), as well as participating in user testing (see Intervention Pilot Study for participant characteristics). Research findings will be disseminated to adolescents and the wider general public via the current industry partner’ and UNICEF’s external communication networks (e.g., social media campaigns).

### Eligibility criteria

The current chatbot is a universal intervention that is designed to provide population-wide benefits, irrespective of an individual’s level of risk. Therefore, increased risk for body image concerns was not an inclusion criterion for this trial. Eligible participants are adolescents aged 13–18 years old; Brazilian Portuguese speaking; Brazilian resident; and, have access to *Facebook Messenger*.

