### The current trial design

This paper outlines the protocol for the co-creation and controlled evaluation of a chatbot targeting risk and protective factors for body image concerns among Brazilian adolescents. A two-arm fully remote randomised controlled trial (Fig. 1) will compare a chatbot intervention to an assessment-only control condition. Participants in the intervention condition will interact with the chatbot over a 72-h period, while participants in the control condition will receive ‘standard care’ for body image concerns among adolescents in Brazil, which at present is no intervention. This protocol paper and the randomised controlled trial design were guided by the Standard Protocol Items: Recommendations for Interventional Trials (SPIRIT; see Fig. 2 and supplementary materials) and the Consolidated Standards of Reporting Trials (CONSORT [28];), including the extension for Electronic Health (CONSORT - EHEALTH [29] see supplementary guidelines).

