4. Development of the digital interface	• The digital interface of the chatbot was constructed by communication and technology experts at Talk2U. • This iterative process involved frequent reviews by adolescents, body image experts based in Brazil and the UK, Dove and UNICEF. • Key design features included: °﻿ The use of *Facebook Messenger*, an instant messaging app for smartphones, to host the chatbot. ° The use of interactive elements that enhance user engagement and saliency of key therapeutic messages, including check-in messages, multi-media stimuli (i.e., audio and video clips; emojis [a small digital image or icon used to express an idea or emotion]), virtual hosts and the gamification of intervention techniques. ° In regards to gamification (i.e., the use of game design elements in non-game contexts, [41]), users needed to successfully complete a technique before progressing to the next technique within a thematic cluster. Gamification is used to incentivise users to continue their engagement while allowing them to master easier skills before progressing to more challenging tasks [42]. The ordering of techniques within each thematic cluster was informed by the researchers’ expertise, as well as feedback from further focus groups with adolescents on the acceptability and feasibility of the techniques and presentation formats. • Project partners with technology and marketing expertise advised on the selection of the chatbot’s name, *Topity*. • To reduce bias the institutional and industry affiliations were not displayed on the user interface. Participants and parents were, however, informed of the multi-international partnership and the relevant organisations involved in the ‘Parent and Participant Information & Consent’ form. • Topity can be accessed via Facebook Messenger using the following URL link: https://www.facebook.com/topitychat/

**Table 2 Tab2:** Chatbot Intervention Topics, Change Techniques and Steps

Topics	Change Technique Objectives	Technique Steps
*Family, friends & body image*		

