#### Intervention pilot study

A pilot study was conducted with 154 Brazilian adolescents to assess *Topity’s* user experience (e.g., ease of use) and acceptability (e.g., enjoyment; content relevance) prior to the main trial. Participants were 13–18-year-old girls and boys (56% girls; *M* = 15.67, SD = 1.62) from geographically diverse regions of Brazil, who were recruited via peer-support leaders, secondary school teachers and non-profit organisation officers known to UNICEF. Following parental consent and participant assent, adolescents were invited to engage with *Topity* as much as they needed over a one-week period. Adolescents assessed the chatbot on 11 acceptability factors, using 7-point response scales (e.g., 1 = *not at all interesting*; 7 = *very interesting*). Factors included: emotive response to the chatbot (e.g., enjoyment, interest, comfortability), relevance (e.g., pertinence, importance and helpfulness of the content to the user and other young people in Brazil), ease of use (e.g., speed and accuracy of responses) and willingness to recommend (e.g., how likely the user would recommend *Topity* to a friend and re-engage in the future). Mean scores for each item, as well as an overall acceptability score are provided in the supplementary materials. Overall, *Topity* was rated highly on overall user experience and acceptability across genders (girls; *M* = 6.40, *SD* = .65; boys; *M* = 6.0, *SD* = 1.03) and age (13–15 years; *M* = 6.41, *SD* = .61; 16–18 years, *M* = 6.07, *SD* = .99). Based on this feedback, no modifications were made to the chatbot prior to the main trial.

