### Participant recruitment and procedure

A community sample of 2800 adolescents aged 13–18 from diverse ethnic, geographic and socio-economic backgrounds will be recruited via a Brazilian research agency’s recruitment panels (i.e., via email to their participant databases) and via UNICEF’s online communication platforms (e.g., U-Report^1^). Recruitment will occur 2 weeks prior to the trial commencing. Given UNICEF’s reach and expertise with underserved adolescents in Brazil, the inclusion of this recruitment channel will ensure that a diverse sample is approached for participation. Further, recruitment numbers across these metrics (e.g., geography) will be regularly monitored and addressed by the research team to ensure diversity across the sample is achieved. Recruitment materials will include a link to an online screener questionnaire to determine participant eligibility. After being screened as eligible, participants will be emailed an information pack to be read with their parent or guardian. Parents will provide consent as per the Brazilian General Data Protection Law, by uploading their signature to online identification verification software that is monitored by the research agency. Following parental consent, adolescents will complete the online self-report assessment (T1), which will commence with adolescents providing informed assent. Those who do no assent will not proceed with the trial. On completion of the survey, adolescents will be randomised into one of two conditions: intervention or assessment-only. Those in the intervention condition will receive a link to the chatbot 24-hours after completing the baseline assessment. Those in the assessment-only condition will be provided with a link to the chatbot after they have completed all assessment timepoints.

Adolescents in the intervention condition will be encouraged to engage with the chatbot as much as possible over a 72-hour period. During this time, participants may complete the eight intervention techniques as many times as they like. Participants will be assessed on state body satisfaction and affect when they first enter the chatbot and immediately after engaging with a technique. If participants do not engage with the chatbot after 12-, 16 and 23.5 hours, they will receive a prompting notification that encourages engagement with the chatbot. That is, if they do not engage after the 12-hour prompt, they will receive up to two more prompts.

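### Controls get the chatbot link only after T4, but earlier Topity users are not excluded, the printed Messenger address has no stated access restriction, and no check of control use before T4 is described

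*Protocol article*

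**What the plan says.** The comparator is described in The current trial design as standard care, "which at present is no intervention". H2 compares change in trait outcomes from T1 to T2, T3 and T4 between that arm and the chatbot arm.

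Eligibility criteria gives four requirements: "Eligible participants are adolescents aged 13–18 years old; Brazilian Portuguese speaking; Brazilian resident; and, have access to" Facebook Messenger. No exclusion is listed.

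Intervention pilot study reports: "A pilot study was conducted with 154 Brazilian adolescents". On age it says "Participants were 13–18-year-old girls and boys", the same range as the trial. They were adolescents "who were recruited via peer-support leaders, secondary school teachers and non-profit organisation officers known to UNICEF", were invited to use Topity over one week, and the chatbot was not changed before the main trial. The trial itself recruits through a research agency's panels and "via UNICEF’s online communication platforms".

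Two safeguards are stated. Participant recruitment and procedure says: "Those in the assessment-only condition will be provided with a link to the chatbot after they have completed all assessment timepoints". The opening of the Discussion places free release to Brazilian adolescents after trial completion, provided the chatbot proves efficacious.

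Table 1 (phase 4) says "Topity can be accessed via Facebook Messenger using the following URL link" and prints the address. It mentions no restriction on who may enter. Table 3 ties the engagement metrics to the 72-hour intervention period and lists no item on use by controls.

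**The concern.** H2 estimates chatbot versus nothing only if controls remain unexposed until T4 and participants start T1 untreated. The stated rules leave two gaps. A pilot participant meets the age criterion, and no listed criterion bars earlier use. A control who comes across the Messenger address may be able to open the chatbot before T4. The bot has to be running during the trial, because the intervention arm uses it for 72 hours and is then encouraged to continue.

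If the chatbot is beneficial, both routes shrink the estimated contrast. The article describes nothing that would show by how much. A smaller-than-expected effect at one month would then be harder to interpret, because the share of exposed controls would be unknown. No later analysis can recover exposure that was not collected.

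**Working it through.** **Inputs**
- Pilot users: 154 (Intervention pilot study).
- Randomised: 2800, 1:1, 25% attrition, two-sided alpha .05, r = .2, ICC .3 to .6, random slope variance .01, .09 and .25 (Statistical power).
- Share c of controls who use the chatbot before T4: not given, so assumed.

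**Step 1: the plan's own power figure**
- Per arm after attrition: 2800 × 0.75 / 2 = 1050, as the article has for one arm.
- Reading r = .2 as a point-biserial correlation: d = 2r/√(1 − r²) = 0.4/√0.96 = 0.408.
- Change-score SD approximated as √(2(1 − ICC) + slope variance). The largest value, at ICC .3 and slope variance .25, is √(1.4 + 0.25) ≈ 1.28.
- Closed-form power is above .99 for every combination tried. This matches the stated > .99 for the cross-level effects. It approximates the article's simulation and does not rerun it.

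**Step 2: pilot route**
- Upper bound on the share: 154/2800 = 0.055, if every pilot user enrolled.
- H2 measures change from T1. A pilot user in the control arm who keeps an earlier gain shows no change, like any other control. A pilot user in the intervention arm has less left to gain. If pilot users gain nothing further and are split evenly between arms, the contrast becomes 0.945 of its true size, so d goes from 0.408 to 0.386. Effective sample is 0.945² = 0.893 of nominal.
- Outer limit if all 154 fell in one arm: 154/1400 = 11%, d = 0.363. Block randomisation makes this unrealistic.
- Power at the planned effect stays above .99 in both cases.

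**Step 3: control use before T4**

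If a share c of controls gains the full effect, the contrast is multiplied by 1 − c and the effective sample by (1 − c)².

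| Assumed c | Contrast retained | Effective sample |
|---|---|---|
| 5% | 0.95 | 0.90 |
| 10% | 0.90 | 0.81 |
| 20% | 0.80 | 0.64 |

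**Step 4: does power suffer?**
- At d = 0.408, power remains above .99 up to c = 40%. At 50% it is about .95 to above .99, depending on the SD used (1.28 or 1).
- At an assumed smaller true effect of d = 0.20 with SD 1.28, power falls from .95 (c = 0) to .92 (5.5%), .81 (20%) and .70 (30%).

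**Step 5: what is recorded on control use**
- Before T4: no question to controls and no log of control entry is described.
- After T4: Participant recruitment and procedure says that controls' use will not be monitored. That sentence covers only the period after the one-month assessment and does not settle what happens before it.

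**The case against.** A reader might infer that nothing keeps controls unexposed and that their use goes unrecorded. The article does not support that.

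- The link is withheld until all assessments are done, and general release comes after the trial.
- Table 1 prints the address for readers of the article. Nowhere is it said that the page was open to anyone during the trial, or that controls were given the address. The Discussion and Data Availability speak of free availability in the future tense.
- The absence of recording is inferred from silence. The chatbot takes state ratings on entry, and its developer delivers data files at trial end. The article does not say whether a control's use would appear in them.
- The consent material is said to outline procedures and name the partner organisations. It is not said to give the chatbot's name or address before randomisation.
- The pilot and the trial share a link to UNICEF but not the same recruitment route. One mention of an internal pilot, in Strengths and future impact, does not mean that its participants enter the trial, since the pilot was run beforehand.
- An article condenses the full protocol, and the screener's items are not shown.

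Most of this stands, and it limits the point to what is stated. What remains is that the article presents its eligibility requirements as a list, and that list admits earlier users. Withholding a link does nothing about pilot participants and is weak protection if the page can be found. Whom the trial enrols and what it measures are design matters that a statistical analysis plan cannot repair afterwards.

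**Conclusion.** The point holds as a limited gap. Earlier Topity users are not excluded, no restriction on chatbot entry is stated, and no check of control use between T1 and T4 is described. If the chatbot works, such exposure biases the H2 contrast toward zero.

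The pilot route is bounded at about 5.5% of the contrast. That assumes all 154 enrol, split evenly, keep their earlier gain and add nothing to it; the real figure is probably lower. The control-use route multiplies the contrast by 1 − c, assuming exposed controls gain the full effect. The documents give no basis for c, so the 5% to 20% range is illustrative.

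A reader might go on to infer that the trial is underpowered, or that contamination could by itself explain a null result. Neither follows. Power at the planned effect stays above .99 up to 40% contamination, and a true effect of the planned size would disappear only with contamination far beyond these figures. The concern is a biased estimate with no means of judging the bias. It is an inexpensive improvement and does not undermine the design.

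**What to change.** 1. Add to the eligibility list and the online screener: no previous use of Topity, including in the pilot or user testing. Placing the name among several other apps would avoid pointing future controls to it.
2. At the end of T4, after the outcome measures, ask control participants whether they used Topity during the study. Report the rate. Keep intention-to-treat as the main analysis and use the rate to interpret it. Hold the answers outside the trait file, as the plan already does for state data, so that analysts stay blinded.
3. Where the platform allows, log or restrict chatbot entry by participant-specific link until the last T4.

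The cost is at most 154 potential recruits from the pilot, one screener question and one survey item. The third step needs some platform work and is optional. Since general release is already planned for after the trial, it need not delay public access.

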### Intervention

#### Intervention development and content

An evidence-based framework guided the development of the chatbot content, structure and format. This framework allowed for collaborative decision-making processes, whereby scientific theory and research, adolescents’ needs and preferences, and the expertise of project partners were considered throughout [33]. Intervention development phases and the key tasks and decision-making processes associated with these phases are reported in Table 1. These phases resulted in a chatbot, *Topity*, designed for delivery on the *Facebook Messenger* platform. The chatbot targets sociocultural risk and protective factors for body image using eight therapeutic techniques derived from cognitive and behaviour theory for body image [43]. The techniques teach adolescents how to critically analyse and evaluate media content to reduce vulnerability to negative media influences [44]; identify and challenge unhelpful thinking styles and behaviours that perpetuate body image distress [43]; and how to appreciate features and functions of the body beyond appearance [45]. A summary of the intervention topics and the associated change techniques are described in Table 2.

**Table 1 Tab1:** Intervention development phases and associated tasks

Phase	Key development tasks and decision-making processes
1. Select and appraise the best available scientific research and evidence.	• Critically evaluated extant literature to identify key risk and protective factors for body image among Brazilian adolescents. • Concurrently, UNICEF conducted 26 workshops with 681 (66% girls) ethnically diverse Brazilian adolescents across 15 northern and south-eastern cities to better understand the nature of, and influences on, their body image, and their preferences for the chatbot’s key messages and persona [34].
2. Apply the evidence in a collaborative decision-making process with relevant parties.	• Data from the literature review and focus groups informed a collaborative decision-making process between academics, industry partners and UNICEF to select which risk and protective factors would be targeted within the chatbot. • Three themes were agreed upon: 1) Unrealistic beauty standards perpetuated by society; 2) Appearance pressures experienced within interpersonal relationships; 3) Acceptance and appreciation of one’s body.
3. Selection and adaptation of extant techniques that target the agreed upon themes, for use in the chatbot.	• A micro-intervention framework was used to identify and select therapeutic techniques that addressed the above themes [35]. • Techniques needed to be brief (e.g., completed in under 10 min), standalone (e.g. a distinct beginning and end), immediately actionable (e.g., can be executed in the moment, without additional resources) and adaptable for digital platforms. • Researchers drew on their expertise of working with evidence-based body image prevention and intervention approaches and a meta-analysis on therapeutic change techniques to identify and select appropriate techniques [31]. • Eight techniques (see Table 2) were extracted from extant evidence-based body image programs, including: *Confident Me* [36], *The Body Image Workbook* [37], and *Expand Your Horizon* [38]. • A script was developed for each technique and was reviewed by body image experts from Brazil and the UK, as well as Dove and UNICEF. • Scripts were then amalgamated into a written interactive dialogue to be delivered by the chatbot fictional hosts, Dandara (a young Brazilian woman) and Gabriel (a young Brazilian man). • Hosts’ gender and persona were informed by: ° Mixed-gender preferences observed among young people receiving body image interventions [39]. ° Adolescents’ use of peers for emotional and informational support in online environments ([40]). ° Qualitative and quantitative data obtained by UNICEF via focus groups and an online survey via UReport with girls and boys name preferences.
4. Development of the digital interface	• The digital interface of the chatbot was constructed by communication and technology experts at Talk2U. • This iterative process involved frequent reviews by adolescents, body image experts based in Brazil and the UK, Dove and UNICEF. • Key design features included: °﻿ The use of *Facebook Messenger*, an instant messaging app for smartphones, to host the chatbot. ° The use of interactive elements that enhance user engagement and saliency of key therapeutic messages, including check-in messages, multi-media stimuli (i.e., audio and video clips; emojis [a small digital image or icon used to express an idea or emotion]), virtual hosts and the gamification of intervention techniques. ° In regards to gamification (i.e., the use of game design elements in non-game contexts, [41]), users needed to successfully complete a technique before progressing to the next technique within a thematic cluster. Gamification is used to incentivise users to continue their engagement while allowing them to master easier skills before progressing to more challenging tasks [42]. The ordering of techniques within each thematic cluster was informed by the researchers’ expertise, as well as feedback from further focus groups with adolescents on the acceptability and feasibility of the techniques and presentation formats. • Project partners with technology and marketing expertise advised on the selection of the chatbot’s name, *Topity*. • To reduce bias the institutional and industry affiliations were not displayed on the user interface. Participants and parents were, however, informed of the multi-international partnership and the relevant organisations involved in the ‘Parent and Participant Information & Consent’ form. • Topity can be accessed via Facebook Messenger using the following URL link: https://www.facebook.com/topitychat/

**Table 2 Tab2:** Chatbot Intervention Topics, Change Techniques and Steps

Topics	Change Technique Objectives	Technique Steps
*Family, friends & body image*		
1. Banish body talk	1. Define and identify forms of body talk. 2. Identify the consequences of body talk and implement strategies for challenging this dialogue.	• User reflects on their own body talk, by estimating the frequency of engagement (e.g., number of times in preceding week), areas of fixation (e.g., belly; legs; skin colour) and the type of commentary (e.g., compliment, criticism, comparison). • Bot led deconstruction task (social media post); user considers the use and frequency of body talk and its impact on the person posting and their followers. • User generates alternative comments that focus on non-appearance aspects in the image (e.g., their affect; the activity, the location); user commits to engaging in this behaviour over the coming week.
2. Dealing with provocative people	1. Identify people that negatively impact your body image. 2. Explore how and when to use assertiveness strategies to address the unhelpful behaviours of others.	• Bot led discussion on how others impact our body image and how these behaviours are framed (e.g., concern, helpful advice, friendly teasing). • User identifies those who negatively impact their body image. • Bot introduces and applies the RIGHTS assertiveness model to an example scenario. • User invited to practice the RIGHTS model with the bot.
*Social media & body image*		
1. The messages behind the media	1. Develop media literacy skills in critically analysing and evaluating media content and the motivations of content creators (e.g., influencers, industry brands). 2. Identify and implement strategies that challenge unrealistic media images and messages, and create safe social media environments.	• Bot led discussion on media literacy; user identifies how media images are manipulated and the motivations of content creators. • Dove Selfie; user watches a 75-second clip on photo editing strategies, indicates their emotive reaction and identifies newly learnt strategies. • Bot describes strategies for creating a realistic, diverse and inclusive social media environment; user commits to engaging in one behaviour in the next week.
2. Unfair-to-compare	1. Define and identify examples of the cognitive distortion, ‘Unfair-to-Compare’. 2. Implement strategies that challenge and reduce upward comparison making.	• Bot led discussion on the internalisation of appearance ideals and upward comparison making. • User reflects on their engagement with this thinking style and the consequences associated with upward comparison making. • Bot describes strategies for challenging the ‘Unfair-to-Compare’ thinking style.
3. A whirlpool of comparisons	1. Identify thoughts and behaviours that contribute to the cycle of comparison making. 2. Identify and implement strategies to stop the cycle from starting or worsening.	• Bot led discussion on the cycle of comparison making; whirlpool analogy. • User identifies their comparison making behaviours and the consequences of these behaviours for themselves and others. • Bot describes strategies for exiting the whirlpool.
4. The magnifying glass	1. Define and identify examples of the cognitive distortion, ‘The Magnifying Glass’. 2. Identify and implement strategies that reduce selective attention on disliked body parts, while increasing attention towards areas that are liked and appreciated.	• Bot led explanation of selective attention and its role in maintaining body image concerns. • User reflects on their areas of fixation (e.g., stomach, legs, body hair). • Bot describes strategies for reducing selective attention. • User invited to engage in a guided mirror exposure task; if unable to in the moment, the audio is saved for a more appropriate time.
*Body appreciation and functionality*		
1. Beauty bound	1. Define and identify examples of the cognitive distortion, ‘Beauty Bound’. 2. Identify and implement strategies that reduce self-imposed body image rules that prevent life engagement.	• Bot led discussion on self-imposed body image rules and limitations; the importance of focusing on the body’s functionality (i.e., what it can do and experience) when attempting to overcome body image rules. • Visualisation activity; user recalls personal example of Beauty Bound thinking (e.g., thoughts, feelings, behaviours and outcome); then visualises the scenario without self-imposed boundaries (e.g., thoughts, feelings, behaviours and outcome); user identifies the differences.
2. Expand your horizon	1. Define body functionality and identify the different forms of functionality. 2. Describe the importance of our own body’s functions.	• Bot led discussion on body functionality (i.e., what the body can do and experience). • Functionality activity; user provided with categories of functionalities and the associated experiences / activities: sensation (i.e., touch, taste, sight); physical activity (e.g., running, cycling, jump-rope), creativity (e.g., cooking, photography, drawing) and self-care (e.g., petting animals, meditation, having a bath). • User selects their most important experience/ activity within each category. • User then reflects on one experience / activity in-depth (e.g., describe what dancing allows the person to experience and why it’s important to them).

